### **6.3.3 Emergency unblinding**

Emergency unblinding might be performed in the event of an emergency situation where it is necessary to know the investigational medical product actually taken by the subject. IWRS is contacted prior to emergency unblinding to determine the group to which the subject is assigned and the dose given. Detailed procedures or training on how to perform code unblinding through the system will be provided to all sites at the start of the study. Whenever possible, CRA or equivalent personnel should be contacted prior to unblinding.

If the code is unblinded, the Clinical Project Manager (CPM) or designee will be notified immediately via the IWRS, but the CPM will remain blinded to specific treatment information. Any unblinding of the IMP by the Investigator must be documented in the source documents and on the study termination eCRF page.

## **6.4 Intervention compliance**

According to the research evaluation schedule 1.2.1, the investigational drug will be administered by the study nurse or the patient his/herself at the time points specified in the protocol.

The study nurse/subjects/their parents/legal representatives must document the subject's medication compliance for each investigational drug administration. For each injection, time compliance is defined as within the dosing time (9:00 a.m.)  $\pm$  3 h. If the drug is dispensed to the subjects and injected outside the hospital, the compliance of injection dose shall be additionally recorded: The patient shall take photos of GanleePen with the dose knob adjusted, which will be collected uniformly to record the injection dose. The investigator will instruct the subject/his or her parent/legal representative to bring back at each visit the vial containing all remaining investigational drug dispensed at the previous visit. The acceptable dose compliance is defined as not exceeding the protocol-specified dose  $\pm$  10%. Dose compliance is calculated as: The amount of drug injected once into the subject/the total amount of drug to be injected once into the subject  $\times$  100%.

If the drug is dispensed to a subject, the investigator will instruct the subject/his or her parent/legal representative to bring back at each visit the vial containing all remaining investigational drug dispensed at the previous visit.

If a subject is found to be persistently non-compliant with treatment (time compliance or dose compliance out of the specified compliance range for 3 times cumulatively), the sponsor will decide with the Investigator whether the subject should be withdrawn from the study.

The quantity of drug dispensed and returned must be recorded in the source documents. Please refer to the drug management manual or injection SOP for specific requirements.

## **6.5 Concomitant therapy**

Any treatment other than the investigational drug, including over-the-counter drugs, must be accurately documented in the source documents and eCRF.

All concomitant medication taken within the three months prior to screening shall be recorded in the eCRF at the screening visit, and thereafter, records shall only be made if there is a change in medication. The corresponding date when any changed administration is initiated shall be recorded in the eCRF.

For all subjects, all changes to their concomitant medications shall be recorded on the pages for concomitant medication of the eCRF, respectively. Such recording shall cover the drug name (generic name, if available, as well as the trade name), indication(s), dosage

---

form, specification, date of administration, usage and dosage.

The above description also applies to non-drug therapy.

Prior and concomitant medications are listed by subject using WHODrug (current effective version) coding and summarized by the Anatomical Therapeutic Chemical (ATC) classification system.

#### **6.5.1 Prohibited concomitant treatment (drug and non-drug therapies) during the trial**

1) GLP-1 receptor (GLP-1R) agonists, GLP-1R/Glucagon Receptor (GCGR) agonists, Glucose-dependent insulintropic polypeptide receptor (GIPR)/GLP-1R agonists or GIPR/GLP-1R/GCGR agonists;

2) Drugs affecting body weight, including systemic steroids (intravenous, oral, or intra-articular administration), Antidepressant such as selective serotonin reuptake inhibitors (SSRIs), serotonin noradrenaline reuptake inhibitors (SNRIs), tricyclics, tetracyclics, etc., other psychiatric agents or sedatives (e.g. imipramine, amitriptyline, mirtazapine, paroxetine, phenelzine, chlorpromazine, thioridazine, clozapine, olanzapine, valproic acid, valproic acid derivatives, lithium salts), diuretic, etc.;

3) Traditional Chinese medicine, Chinese patent drug, herbal medicine, health-care products, meal replacements, etc. that affect body weight;

4) Weight loss drugs, such as sibutramine hydrochloride, orlistat, phentermine, phenylpropanolamine, mazindol, phentermine, diethylpropion, lorcaserin, phentermine/topiramate, naltrexone/bupropion, etc.;

5) Hypoglycemic agents, such as metformin,  $\alpha$ -glucosidase inhibitors, sulfonylureas, DPP-4 inhibitors, SGLT-2 inhibitors, thiazolidinediones (TZDs), insulin, insulin analogs, etc.;

#### **6.5.2 Allowable concomitant treatment (drug and non-drug therapies) during the trial**

If the investigator judges it necessary to use non-prohibited concomitant treatment (drug and non-drug therapy), the investigator shall truthfully record such information as name, duration, and dosage.

---

## **7. Assessments and procedure in the clinical trial**

### **7.1 Safety assessments**

#### **Physical examination**

Physical examinations will be performed at the time points specified in the study assessment schedule, including: General condition, skin, neck (including thyroid), head, chest, abdomen, back, lymph nodes, the four limbs, and nervous system.

#### **Fundus examination**

Fundus examination will be performed at the time points specified in the study assessment schedule. Fundus examination results will be recorded as “normal”, “abnormal but not clinically significant”, or “abnormal and clinically significant”. The “abnormal and clinically significant” will be defined as AE.

#### **Vital signs**

Vital signs, including the following, will be measured at the time points specified in the study assessment schedule:

- Blood pressure (mmHg), measured at rest;
- Breath rate (breaths per min);
- Pulse (times per min)
- Body temperature (°C).

#### **Electrocardiogram**

Standard resting 12-lead ECGs will be documented for subjects at the time points specified in the study assessment schedule. The results of ECG recordings will be included in the CRF. The source ECG recording will be evaluated by the investigator using automated measurements and the results will be interpreted according to the categories of normal, abnormal but not clinically significant, and abnormal and clinically significant. An ECG is defined as an AE only if it is assessed as abnormal and clinically significant.

#### **Hypoglycaemic episodes and treatment plan**

In this study, hypoglycaemia is defined as a blood glucose level below 3.0 mmol/L. Once a hypoglycaemic event is observed, it is graded according to CTCAE 5.0, and classified as either an AE or SAE. The following classification of hypoglycaemia will be used if the blood glucose can be measured:

- Grade 1: < lower limit of normal–55 mg/dL; < lower limit of normal–3.0 mmol/L;
- Grade 2: <55–40 mg/dL; <3.0–2.2 mmol/L;
- Grade 3: <40–30 mg/dL; <2.2–1.7 mmol/L;

- 
- Grade 4: <30 mg/dL; <1.7 mmol/L; life-threatening; epileptic seizure;
  - Grade 5: Death.

If the subject experiences symptoms of hypoglycaemia, but his/her blood glucose is not measured or his/her blood glucose  $\geq 3.0$  mmol/L, investigators need to comprehensively determine whether it is a hypoglycemic event; If it cannot be determined, AE can be recorded separately based on symptoms. The subject who develops a hypoglycaemic reaction may have the following clinical manifestations: palpitations, asthenia, starvation, sweating, pallor and shakiness of hands and feet, etc.; in such a case, the doctor should be informed immediately.

Severe hypoglycaemia is defined if the following criteria are met: hypoglycaemia without specific blood glucose limits, with severe cognitive dysfunction and requiring additional measures to help recover.

Hypoglycemia treatment plan is as follows:

For conscious subjects: The investigator may provide the subjects with carbohydrate food (such as steamed bread, dessert, biscuits, etc.), oral glucose or sucrose, etc. For unconscious subjects: the investigator may establish intravenous access to administrate intravenous glucose as prescribed by the doctor. During the treatment, attention should be paid to the changes of consciousness, speech clarity, body movements and cognitive function. Blood pressure, heart rate, breath rate, and skin color of the subjects should be monitored as well as their blood glucose for any changes to ensure the safety of subjects, and keep them warm. At the same time, medical records and hypoglycemia event reports shall be recorded.

According to the experimental flow chart, the investigator recorded the occurrence of hypoglycemia-related events according to the trial flow chart, if any, in the Hypoglycemic Event Form in the original medical records, and recorded them in the eCRF as well. Information to be recorded includes: Date, time of hypoglycaemic episode, time of last meal before episode, whether there are any symptoms at the time of episode, whether it is self-treatable, and the blood glucose level before treatment (if any).

#### **Hypoglycemia treatment plan is as follows:**

For conscious subjects: The investigator may provide the subjects with carbohydrate food (such as steamed bread, dessert, biscuits, etc.), oral glucose or sucrose, etc. For unconscious subjects: The investigator may establish intravenous access to administrate intravenous glucose as prescribed by the doctor. During the treatment, attention should be

paid to the changes of consciousness, speech clarity, body movements and cognitive function. Blood pressure, heart rate, breath rate, and skin color of the subjects should be monitored as well as their blood glucose for any changes to ensure the safety of subjects, and keep them warm. At the same time, medical records and hypoglycemia event reports shall be recorded.

According to the study process table, the investigator should record the occurrence of hypoglycemia-related events, if any, in the Hypoglycemic Event Form in the original medical records. Information to be recorded includes: Date, time of hypoglycaemic episode, time of last meal before episode, whether there are any symptoms at the time of episode, whether it is self-treatable, and the blood glucose level before treatment (if any).

### **Pancreatitis**

If acute or severe & persistent abdominal pain consistent with characteristics of acute pancreatitis occurs, IMP should be interrupted until pancreatitis is ruled out. The investigator may arrange follow-up examinations based on the specific conditions according to national guidelines, expert consensus and diagnosis and treatment specifications such as *Expert Consensus on Emergency Diagnosis and Treatment of Acute Pancreatitis* issued by Chinese Society for Emergency Medicine of Chinese Medical Association, *Guidelines for diagnosis and treatment of acute pancreatitis in China (2021)* issued by Chinese Pancreatic Surgery Association, Chinese Society of Surgery, Chinese Medical Association. If acute pancreatitis is excluded, the subject may be re-enrolled at the discretion of the investigator.

### **Allergic reactions**

In the event of a possible IMP-related severe acute allergic reaction during the study, blood will be drawn for test of trypsin (total and activated) within 3 h following the onset of the allergic reaction. Blood should be drawn for anti-GZR18 IgE antibodies and anti-GZR18 binding antibodies and trypsin after a washout period of at least 5 weeks.

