### **Clinical laboratory tests**

Blood will be drawn for hematology, blood biochemistry (fasting), coagulation, lipase, amylase, and TSH/FT3/FT4 at the time points specified in the study assessment schedule. Midstream urine should be collected for urinalysis. The above indexes are all tested in the Department of Clinical Laboratory of the sub-site (hospital).

Blood will be drawn for calcitonin at the time points specified in the study assessment schedule. Based on available data from rodent experiments with other GLP-1 analogs, this class of drugs has a risk of causing thyroid C-cell tumors. But the findings in rodents have

not been observed in non-human primates and are not considered related to humans. However, as a precaution, calcitonin levels in the blood need to be measured during the trial (calcitonin concentrations have been proven to be related with the thyroid function in rodent models). Calcitonin will be tested by the Department of Clinical Laboratory of the sub-site.

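### Section 7.1 twice orders trypsin in the work-up of a severe allergic reaction, where the sampling scheme fits the mast-cell marker tryptase; most likely a wording or translation slip

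*Protocol*

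**What the plan says.** The protocol's section 7.1, under Allergic reactions, has two sentences on this. The trigger is stated as "In the event of a possible IMP-related severe acute allergic reaction during the study". For the acute sample, "blood will be drawn for test of trypsin (total and activated) within 3 h following the onset of the allergic reaction". For the later sample, blood is to be drawn for "anti-GZR18 IgE antibodies and anti-GZR18 binding antibodies and trypsin after a washout period of at least 5 weeks".

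Two neighbouring parts of section 7.1 deal with the pancreas. Clinical laboratory tests sets the scheduled panel: "Blood will be drawn for hematology, blood biochemistry (fasting), coagulation, lipase, amylase, and TSH/FT3/FT4". Pancreatitis handles a suspected episode separately: "The investigator may arrange follow-up examinations based on the specific conditions according to national guidelines, expert consensus and diagnosis and treatment specifications". Neither names trypsin.

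Section 8.8 (Biological samples) leaves collection, processing, storage and shipment details to a sample handling manual or corresponding documents, which are not available here.

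**The concern.** The analyte does not match the purpose of the paragraph. After a severe acute allergic reaction, the question for a marker enzyme is whether mast cells were activated. Trypsin, which comes from the pancreas, does not answer that; tryptase, which mast cells release, does. The two names differ by a few letters and are easily confused in translation.

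The stake is one piece of evidence per event. The acute sample is tied to a 3-hour window and cannot be taken again. If the wrong assay is run on it, the acute value of the mast-cell marker is missing for that subject, and a trypsin value obtained after washout is no baseline for it. The drug is a modified peptide, and the protocol lists immunogenicity among its secondary objectives, so it is reasonable to want any severe reaction properly characterised.

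**Working it through.** No arithmetic tests this point. The check is a comparison of the text with itself, plus one fact of general biochemistry: trypsin is a pancreatic digestive protease, and tryptase is a mast-cell protease.

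**Step 1: is it an isolated misprint?** No. The same word stands in both sentences of the paragraph, once for the acute sample and once for the post-washout sample. Tryptase does not appear in the protocol text available, including the abbreviations list and the flowchart notes in section 1.2. Nothing elsewhere corrects the term.

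**Step 2: do the elements of the paragraph fit the named analyte?**

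| Element in section 7.1, Allergic reactions | Read as trypsin | Read as tryptase |
|---|---|---|
| Triggered by a severe acute allergic reaction | No stated reason to measure it | Fits |
| Sample within 3 h of onset | No stated reason | Fits an acute mast-cell marker |
| Total and activated forms requested | No stated reason in an allergy work-up | Fits |
| Repeat after at least 5 weeks of washout | No stated reason | Fits an acute-against-baseline pair |
| Repeat drawn with anti-GZR18 IgE | No link | Fits a question about IgE and mast cells |

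**Step 3: could trypsin be a deliberate pancreatic check?** Nothing supports that. Scheduled pancreatic monitoring uses lipase and amylase. A suspected pancreatitis has its own paragraph, with its own trigger (abdominal pain) and a reference to guidelines. Trypsin is in neither, and no passage gives an allergy-related reason for it.

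**Step 4: are similar slips present?** Yes, which makes a translation error plausible. Section 9.5 speaks of pharmacogenetic parameters from a non-atrial model where pharmacokinetic parameters are being calculated in WinNonlin. Section 9.8 writes *degree of grasp* where the synopsis has power. Later sections expand CA as Certificate Authority, while the abbreviations list gives Competent authority.

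**Step 5: what would be lost, and what would not?**
- Lost, if the text is followed literally: the acute mast-cell marker and its post-washout comparison value, for each affected event.
- Kept: anti-GZR18 IgE and binding antibodies from the same post-washout draw, and scheduled ADA and NAb at W0, W16, W30 or early termination, and W33.
- Unaffected: severity grading (CTCAE v5.0) and the causality table in section 7.4, neither of which uses the enzyme; the endpoints in section 3.2; the analyses in sections 9.3 to 9.5.

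**Step 6: how many subjects could be concerned?** Table 6-1 plans 4 × 52 + 65 = 273 subjects on GZR18 and 5 × 13 = 65 on placebo, together 338. Because the trial is double-blind within each dose group, the work-up could be triggered in any of the 338. The protocol gives no expected rate of severe allergic reactions, so no event count can be derived. That they will be few is an assumption.

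**The case against.** The strongest reply is that this may be only a translation slip in an English text, with no consequence at the sites. The trial runs in about 24 Chinese centres, the language of their working documents is not shown, and the sample handling manual may already name the right assay. That stands as a limit on the consequence: wrong testing follows from the text as written but is not shown to happen. It does not make the text right, because section 7.1 is an instruction to sites and nothing visible overrides it.

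A reader might go further and infer that the loss of information for each event is complete, or that the 5-week sample becomes useless. The protocol does not support this. The post-washout draw also supplies drug-specific IgE and binding antibodies, so sensitisation to the drug is still assessed; only the enzyme part of that sample would be of no use.

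A reader might also fear that a raised trypsin would be taken for a pancreatic signal. That is speculation. The test is triggered only by an allergic reaction, and pancreatic monitoring rests on other enzymes.

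Finally, allergic reactions are not among the adverse events of special interest, which are hypoglycaemia and gastrointestinal events, and no endpoint depends on this test. That is correct, and it keeps the point small.

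**Conclusion.** The point holds as an error of terminology in an operational instruction. Section 7.1 twice names an analyte that does not fit the paragraph's purpose, while every other element of the paragraph fits tryptase. Followed literally, the text would cost the biochemical evidence of mast-cell activation for each severe acute allergic reaction, and that evidence could not be recovered afterwards. Drug-specific antibody evidence would remain.

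The primary endpoint, sample size, error rate and planned analyses are untouched. The point is worth correcting because the affected sample cannot be repeated and the correction is nearly free.

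The conclusion assumes the general biochemistry above, that no unseen document already corrects the term for the sites, and that the English text reflects the instruction they follow. It would not be safe to conclude that every such event in the trial was in fact tested with the wrong assay.

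**What to change.** Confirm with the sponsor which analyte was intended, checking the original-language text if there is one. If it is tryptase, as the scheme indicates, replace trypsin with tryptase in both sentences of section 7.1, Allergic reactions. Then check that the sample handling manual and the kits name the same assay for the acute and the post-washout samples, so that the two values can be compared.

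The cost is one word changed in two places and one check of the manual. The number of samples, their timing, the antibody tests and the treatment of subjects stay as they are.

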### **Clinical laboratory tests**

Blood will be drawn for hematology, blood biochemistry (fasting), coagulation, lipase, amylase, and TSH/FT3/FT4 at the time points specified in the study assessment schedule. Midstream urine should be collected for urinalysis. The above indexes are all tested in the Department of Clinical Laboratory of the sub-site (hospital).

Blood will be drawn for calcitonin at the time points specified in the study assessment schedule. Based on available data from rodent experiments with other GLP-1 analogs, this class of drugs has a risk of causing thyroid C-cell tumors. But the findings in rodents have

not been observed in non-human primates and are not considered related to humans. However, as a precaution, calcitonin levels in the blood need to be measured during the trial (calcitonin concentrations have been proven to be related with the thyroid function in rodent models). Calcitonin will be tested by the Department of Clinical Laboratory of the sub-site.

### **Injection site observation**

The injection site will be observed for abnormalities at the time points specified in the study assessment schedule, as judged by the subject's chief complaint and the physical examination by the investigator.

### **Immunogenicity**

Blood will be drawn for immunogenicity, including GZR18 anti-drug antibodies (ADA) and neutralizing antibodies (NAb) at the time points specified in the study assessment schedule.

### **Mental health conditions**

Conduct C-SSRS questionnaire and PHQ-9 questionnaire evaluation according to the specified time points in the experimental flowchart, record the mental health status of the subjects, and refer to Attachment 7 and Attachment 8 for detailed questionnaire content.

## **7.2 Efficacy assessment**

### **Body measurements**

Body measurements will be performed at the time points specified in the study assessment schedule, including the height (cm), weight (kg), waist, hip circumference and calculated BMI ( $\text{kg/m}^2$ ) and waist circumference (cm). During measurement, subjects shall with their shoes and coat removed, and shall be fasted with bladder emptied. Please refer to Attachment 5 for specific operations.

### **Quality of Life Assessment**

Conduct SF-36 questionnaire and IWQoL Lite CT questionnaire evaluations according to the specified time points in the experimental flowchart, record the quality of life of the subjects, and refer to Attachment 9 and Attachment 10 for detailed questionnaire content.

## **7.3 Pharmacokinetic evaluation**

One of the secondary objectives of this trial is to assess the pharmacokinetics (PK) of continuous doses of GZR18 by determining the concentration of GZR18 in plasma.

Blood samples will be collected at the time points specified in the study assessment schedule, and the exact time of blood sampling will be documented in the original medical records. PK samples are tested and analyzed by a third-party testing company.

